**Methods:**

We created the Reducing Emotional Distress for Childhood Hypoglycemia in Parents (REDCHiP) intervention by merging age-appropriate T1D education and behavioral parenting strategies with cognitive behavioral therapy strategies that are effective for reducing fear and promoting adaptive coping. REDCHiP uses 10 video-based telehealth sessions that are a combination of group and individual sessions. We will recruit up to 180 families of young children with T1D to participate in this clinical trial from two pediatric diabetes clinics located in the midwestern and southern United States. Once families have been enrolled, we will randomize caregivers based on child age (age 2-3 years or 4-5 years), child sex, and family CGM use to participate in the REDCHiP or attention control intervention. Families will complete 3 assessment visits that coincide with study entry, end of treatment, and 3-month posttreatment. At each assessment visit, we will collect questionnaire data from caregivers, accelerometry data from caregivers and children, CGM data from children, and a blood sample to measure glycated hemoglobin levels from children.

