### Randomization

This study will use a 2-arm randomized attention control design with 90 families recruited to each of the REDCHiP and attention control intervention conditions. We will stratify caregivers based on their child’s sex, child age (2 to 3 years versus 4 to 5 years) and CGM use (CGM or no CGM) and randomize to condition using blocks of eight. Recruitment and randomization will occur simultaneously across all participating sites using site-specific randomization envelopes prepared by the study biostatistician. This strategy will allow us to populate groups using caregivers from any site, thereby improving our recruitment efficiency and minimizing possible clinic effects.

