### Data Analysis Plan

We will measure parenting stress and caregiver fear of hypoglycemia using the Pediatric Inventory for Parents [64] and the Hypoglycemia Fear Survey–Parents of Young Children [15,26], respectively. We will use child HbA_1c_ levels and percentage of time in range (eg, 70 to 180 mg/dL) to examine child glycemic control and glycemic variability, respectively. To test for treatment outcomes, we will model study visit 2 scores as a function of visit 1 scores, condition (REDCHiP versus attention control intervention), and selected covariates (eg, race/ethnicity, pump use) in mixed models that include a random intercept to account for clustering of participants within group cohorts. We will accommodate nonnormal outcome variables with log transformation, modeling with an appropriate generalized mixed model or nonparametric test. We will test the effect of condition based on whether the 95% confidence interval for the condition coefficient includes zero (equivalent to a 2-sided test at α=.05). To determine long-term treatment effects, we will test for sustained improvement on outcome variables by modeling scores at study visit 3 as a function of visit 1 scores and condition (REDCHiP versus attention control intervention). To control the overall rate of type I errors, we will conduct these analyses only for variables with a statistically significant condition effect in our primary analysis of treatment outcomes.

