## Discussion

### Limitations

This trial will focus on families of young children with T1D and exclude children who are on conventional insulin therapy, which could limit some of its generalizability. However, we anticipate little negative impact from this decision because intensive insulin therapy is now the gold standard regimen for individuals with T1D. An examination of maintenance effects of REDCHiP up to 3 months’ posttreatment will occur, but we will not be able to draw inferences regarding longer term effects. Our trial includes numerous outcome measures, which increases the risk of missing data. We have attempted to reduce the risk of missing data through device use (eg, accelerometry to measure physical activity and sleep) and online questionnaire access and data sharing. We intend to give caregivers free and accessible technology support before and during telehealth visits in order to reduce any disruptions due to difficulties with the telehealth platform. We intend to stratify our samples according to child sex, age, and CGM status to control for any effect of these variables in our final models. Yet there may be other demographic variables we will not be able to control for a priori that moderate caregiver fear of hypoglycemia, and we may need to adjust for those in our final analyses. In addition, we intend to identify whether young children are using a hybrid closed loop or predictive low-glucose management system via caregiver report or electronic health record review and may adjust for these variables in our final analyses.

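### The outcome models name none of the randomization factors (child sex, age band, CGM use, and site through the envelopes), so intervals are modestly too wide if those factors are prognostic

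*Protocol article*

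**What the plan says.** In the protocol article, the Randomization section says the trial will "stratify caregivers based on their child’s sex, child age (2 to 3 years versus 4 to 5 years) and CGM use" and "randomize to condition using blocks of eight". Allocation is made "using site-specific randomization envelopes prepared by the study biostatistician". The Abstract gives recruitment as "from two pediatric diabetes clinics located in the midwestern and southern United States".

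The Data Analysis Plan models the visit 2 score on the visit 1 score, condition and "selected covariates (eg, race/ethnicity, pump use) in mixed models that include a random intercept to account for clustering of participants within group cohorts". The two examples given are not variables on which the trial stratifies. For visit 3 it lists the visit 1 score and condition only, and it limits that analysis to outcomes with a significant condition effect at visit 2.

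The Limitations section states the intention to "stratify our samples according to child sex, age, and CGM status to control for any effect of these variables in our final models". It then says that other demographic variables might need adjustment. For hybrid closed loop and predictive low-glucose systems, it says the authors "may adjust for these variables in our final analyses".

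**The concern.** Balanced allocation within strata keeps differences between strata largely out of the comparison of arms. A model without the strata leaves that variation in its residual. Its standard error therefore counts variance that the design has already removed. The estimate is unbiased, but the interval is wider than it should be and the test rejects too rarely under the null.

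The effect carries forward, because an outcome that narrowly misses significance at visit 2 is not tested at visit 3. The sections also leave it unclear whether sex, age and CGM status are meant to be in the model at all. Site is mentioned in neither the Data Analysis Plan nor Limitations as a model term.

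**Working it through.** **Sections side by side.** Randomization declares three binary factors, so 2 × 2 × 2 = 8 strata. Separate envelopes at two clinics make site a fourth factor in effect, giving 16 cells. The visit 2 model names none of the four. The visit 3 model names no covariates beyond the visit 1 score, and the Power Analysis model likewise has only baseline and condition. The cohort random intercept cannot stand in for site, because Randomization lets groups be filled with caregivers from any site.

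**Inputs from the Power Analysis section.** 180 families with 20% attrition, and 180 × 0.8 = 144, as stated; 40 cohorts, 20 per arm, averaging m = 144/40 = 3.6; intraclass correlation .10; baseline correlation .72; two-sided α = .05.

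**Assumed, not in the article.** R² is the share of within-cohort residual variance, after the visit 1 score, that the four factors explain; the range shown is 0 to .30. The factors are taken as independent and evenly split.

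**The plan's own power figures.** They do not bear on interval width, but they decide how to show power. The error scale is not stated. The 85% at 0.4 SD is reproduced at 144 families if the outcome variance within condition is 1 (85% to 86%). The 83% at 0.6 SD is not reproduced on any of four scales tried (89% to 99.9%). Power is therefore given below on two scales.

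**Closed form.** With residual variance 1, the cohort variance is .10 and the within-cohort variance is .90.

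- Reported without the factors: Var = 2(.10 + .90/3.6)/20 = 2(.35)/20 = .0350, SE = .187.
- With the factors: Var = 2(.10 + .90(1 − R²)/3.6)/20.
- R² = .10: 2(.10 + .225)/20 = .0325, SE = .180, ratio .187/.180 = 1.04.
- R² = .20: 2(.10 + .200)/20 = .0300, SE = .173, ratio .187/.173 = 1.08.

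The ratio does not depend on the error scale, which cancels.

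**Simulation.** 144 families, permuted blocks of 8 in 16 cells, 20 cohorts per arm, 1500 data sets per scenario, random-intercept model fitted with and without the four factors:

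| R² | CI width, without / with | Type I error without | Type I error with |
|---|---|---|---|
| 0 | 1.00 | 4.9% | 4.9% |
| .05 | 1.02 | 4.7% | 5.0% |
| .10 | 1.04 | 4.5% | 5.0% |
| .20 | 1.08 | 3.9% | 5.1% |
| .30 | 1.13 | 2.9% | 5.3% |

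**Where the excess lies.** At R² = .20 the unadjusted model reports a mean SE of .188, while the true spread of its estimate is .177, so the reported SE is .188/.177 = 1.06 times too large. The adjusted estimate has a spread of .174, and .177/.174 = 1.02. Most of the excess is in the reported SE and little is in the estimate itself.

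**Power at 0.4 SD, without → with the factors.** With outcome variance 1: 85% → 87% at R² = .10 and 87% → 90% at R² = .20. With residual variance 1: 56% → 58% and 56% → 62%.

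**The case against.** The best defence is that omission is not shown. The covariate list in the Data Analysis Plan is introduced as examples, so a factor that is not named is not excluded. The Limitations sentence can be read as promising that sex, age and CGM status will be in the final models. That reading is possible. It is less natural in context, because the next sentence contrasts variables that cannot be controlled in advance and may need adjustment, which suggests that stratifying is itself the control. It also does not reach the visit 3 model, which is given without an open list, or site, which neither section puts in a model. On either reading the two sections need to be reconciled.

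Four stronger inferences are tempting, and the article does not support them:

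- **Covariates chosen after the data are seen.** The wording leaves some adjustment open, but nothing says when the choice is made, and a separate analysis plan may fix it.
- **Closed-loop status taken after randomization.** Limitations gives no time point for it, and Table 3 schedules caregiver report of the insulin regimen at visit 1, before sessions begin.
- **Precision thrown away.** The spread of the unadjusted estimate is within about 2% of the adjusted one at R² = .20. Stratification has already delivered most of its benefit.
- **Race/ethnicity and pump use do not belong in the primary model.** That is a matter of preference. Baseline covariates may stay there if they are named in advance.

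It is also fair that the harm is conservative and conditional. The visit 1 score, with a correlation of .72, is already in the model and may leave these factors little to explain.

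**Conclusion.** The point holds in a limited form. The factors that govern allocation are not named in the visit 2 model and are absent from the visit 3 model as written; site is in neither. Limitations does not resolve this. The consequence is a reported interval that is too wide and a conservative test, without bias and without type I inflation. At 144 families with cohort clustering, the excess width is about 4% if the factors explain 10% of residual variance and about 8% at 20%, with type I error of about 4.5% and 3.9%. Those shares are assumptions, and at zero there is no loss. Treating site as a randomization factor is an inference from the site-specific envelopes, though a reasonable one.

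**What to change.** State the visit 2 and visit 3 models in the same form: visit 1 score, condition, child sex, age band, baseline CGM use and site as fixed effects, with the cohort random intercept. Amend Limitations to say that the stratification factors are included as model terms, so that it agrees with the Data Analysis Plan. List any further covariates, including race/ethnicity, pump use and closed-loop use if wanted, before unblinding and restrict them to pre-intervention values. Label all other adjustment as sensitivity analysis.

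The cost is wording and four degrees of freedom. No new data are needed: the three declared factors and site are known at randomization.

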### Objectives

The aims of this randomized clinical trial are to (1) evaluate whether caregivers who receive the REDCHiP intervention report reductions in parenting stress and fear of hypoglycemia immediately posttreatment compared with caregivers who receive the attention control intervention; (2) evaluate whether children of caregivers who receive the REDCHiP intervention have lower HbA_1c_ and less glycemic variability posttreatment compared with children of caregivers who receive the attention control intervention; and (3) examine whether maintenance reductions in parenting stress and caregiver fear of hypoglycemia and child HbA_1c_ occur 3 months’ posttreatment for families receiving the REDCHiP intervention. Based on preliminary data, our primary hypotheses are (1) caregivers who receive REDCHiP will report reductions in parenting stress and fear of hypoglycemia compared with caregivers who receive the attention control intervention and (2) children of caregivers who receive REDCHiP will achieve more optimal glycemic control than children of caregivers who receive the attention control intervention.

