**Caregiver**			
	Hypoglycemia fear	Calculate total, worry, and behaviors scores from the HFS-PYC^f^ [15,26]	Visits 1, 2, 3
	Parenting stress	Calculate stress frequency and stress difficulty scores from the PIP^g^ [64]	Visits 1, 2, 3
	Depressive symptoms	Calculate total score from the CES-D-R^h^ [65]	Visits 1, 2, 3
	Anxiety	Calculate total score from PROMIS-A^i^ [66]	Visits 1, 2, 3
	Psychopathology	Calculate the depression, anxiety, and somatization scores and the Global Severity Index from the BSI-18^j^ [67]	Visits 1, 2, 3
	Sleep	Calculate TST, sleep latency, and sleep efficiency (TST/total time in bed) using accelerometer data; caregivers will also complete an online sleep log and the PROMIS-S^k^ [68], and we will calculate total score	Visits 1, 2 (Visits 1, 2, 3 for PROMIS-S)
	Treatment satisfaction	Calculate total score from the Treatment Satisfaction Questionnaire	Visit 2

^a^T1D: type 1 diabetes mellitus.

^b^CGM: continuous glucose monitor.

^c^TST: total sleep time.

^d^G8 analyzer: G8a High-Performance Liquid Chromatography Hemoglobin A_1c_ Analyzer (Tosoh Bioscience Inc).

^e^FreeStyle Libre Pro: FreeStyle Libre Pro Flash Glucose Monitoring System (Abbott Laboratories).

^f^HFS-PYC: Hypoglycemia Fear Survey–Parents of Young Children.

^g^PIP: Pediatric Inventory for Parents.

^h^CES-D-R: Center for Epidemiological Studies–Depression Scale Revised.

^i^PROMIS-A: Patient-Reported Outcomes Measurement Information System–Anxiety short form.

^j^BSI-18: Brief Symptom Inventory–18.

^k^PROMIS-S: PROMIS Sleep Disturbance and Sleep-Related Impairment.

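### The rule said to control the overall type I error restricts only the visit 3 tests; the visit 2 outcomes are each still tested at two-sided .05

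*Protocol article*

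**What the plan says.** In the protocol article, Data Analysis Plan, the visit 2 analysis is run outcome by outcome: "we will model study visit 2 scores as a function of visit 1 scores, condition (REDCHiP versus attention control intervention), and selected covariates". The decision rule is: "We will test the effect of condition based on whether the 95% confidence interval for the condition coefficient includes zero", described as "equivalent to a 2-sided test at α=.05". The section names four outcomes: parenting stress (PIP), fear of hypoglycemia (HFS-PYC), HbA1c for glycemic control, and time in range for glycemic variability.

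Visit 3 scores are then modelled in the same way, with this restriction: "To control the overall rate of type I errors, we will conduct these analyses only for variables with a statistically significant condition effect" at visit 2.

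Under Objectives there are two primary hypotheses. The first is that "caregivers who receive REDCHiP will report reductions in parenting stress and fear of hypoglycemia compared with caregivers who receive the attention control intervention". The second concerns more optimal glycemic control in the child. Glycemic variability appears in aim 2 but is not named in either primary hypothesis.

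Table 3 derives more than one score from each caregiver instrument: "Calculate total, worry, and behaviors scores from the HFS-PYC" and "Calculate stress frequency and stress difficulty scores from the PIP". The article does not say which score carries the test.

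**The concern.** The restriction works within a variable, from visit 2 to visit 3. Multiplicity in the main efficacy claims arises across variables at visit 2, where the restriction does not act. The article gives no order of testing, no split of alpha, no single primary outcome and no rule for combining outcomes.

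A reader of the final report would be told that the overall error rate was controlled. Yet efficacy could be claimed on whichever of several outcomes had an interval excluding zero. The Power Analysis also uses .05 for one generic outcome, so it makes no allowance for multiplicity.

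**Working it through.** **Inputs.** Per-test level .05, two-sided (Data Analysis Plan). Number of tests: three constructs in the primary hypotheses (stress, fear, HbA1c as the measure of glycemic control), or four with time in range. Correlations between outcomes are not given, so they are assumed and varied below. The article states no familywise figure to reproduce; its only figure is the per-test .05, which is what a 95% interval implies.

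**What the restriction does.** A visit 3 rejection is possible only where visit 2 was already rejected for the same variable. The event of any rejection at visit 2 or at restricted visit 3 is therefore the same event as any rejection at visit 2. Simulation with four independent outcomes, all nulls true, and correlation of .5 or .72 between visits:
- visit 2 alone: 18.5-18.6%
- visit 2 plus restricted visit 3: the same
- visit 2 plus unrestricted visit 3: 29-32%

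The restriction removes the extra error from visit 3 and leaves the visit 2 rate where it was.

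**Any one significant outcome supports a claim, all nulls true.** Under independence the rate is 1 − .95^k.

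| Tests | Independent | Common correlation .3 | Common correlation .5 |
|---|---|---|---|
| 3 | 1 − .95³ = 14.3% | 13.6% | 12.5% |
| 4 | 1 − .95⁴ = 18.5% | 17.4% | 15.6% |

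For four outcomes at a common correlation of .7 the rate is 13.0%.

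**Hypothesis 1 needs both caregiver outcomes, HbA1c separate and independent.** The probability that both caregiver tests are falsely significant is .05² = .0025 if they are independent, and about .0165 at correlation .7.
- Independent: 1 − (1 − .0025)(.95) = 5.2%
- Correlation .7: 1 − (1 − .0165)(.95) = 6.6%

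This is about 5-7%. If time in range also supported a separate claim, the factor .95² replaces .95 and the range is about 10-11%.

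**All scores of the two caregiver instruments tested.** Three HFS-PYC scores, two PIP scores, HbA1c and time in range make seven. Independence gives 1 − .95⁷ = 30.2%. If the HFS-PYC total is taken as the equal-weight sum of worry and behaviors, the rate is 27.9% with everything else independent, and 22-26% under the other correlation patterns tried.

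**With an adjustment.** Four tests at .05/4 = .0125 give 1 − (1 − .0125)⁴ = 4.9% if independent, and 4.0-4.9% under the correlations tried.

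**The case against.** The strongest reply has three parts.

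First, the restriction does useful work. It is a valid two-step sequence within each variable, and without it the four-outcome rate would rise to about 29-32%. On that reading the sentence is too broad rather than empty. This stands, and it is why narrowing the sentence is an acceptable minimum repair.

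Second, an article may leave to the analysis plan which PIP or HFS-PYC score leads and whether hypothesis 1 needs both outcomes. This also stands, and neither gap is a finding by itself. But the article does not stay silent on error control. It names a mechanism and a purpose, and the mechanism cannot achieve the purpose at visit 2.

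Third, the size depends on the reading. A reader might infer that the primary hypotheses cover four outcomes, so that 16-19% is the error rate of a primary claim. Objectives does not support that: glycemic variability is in aim 2 only, so the primary hypotheses give three constructs and 14.3% or less. A reader might also infer a rate of 30% from testing every listed score. Table 3 lists what will be calculated, not what will be tested as primary, and it contains many more than seven scores. The 30% is an independence ceiling for one particular set of seven.

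**Conclusion.** The point holds as a wrong statement in the text. The rule presented as controlling the overall type I error limits only the visit 3 tests, and the visit 2 family remains unadjusted.

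If any one outcome suffices, the false-positive rate is 14.3% (three constructs) or 18.5% (four outcomes) under independence, and about 12.5% or 15.6% at an assumed correlation of .5. It is about 5-7% if hypothesis 1 requires both caregiver outcomes and HbA1c is the only other claim. The wording of hypothesis 1 permits that reading, but no decision rule states it. Testing all seven scores gives about 22-28% under plausible correlation. All of these figures assume that every null hypothesis is true, and the correlations are assumptions.

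A reader might go further and conclude that HFS-PYC total must be the sole primary outcome because the control arm's parent training is aimed at parenting stress. The article does not say that it is, and Table 1 shows behavioral parent training in REDCHiP too. HFS-PYC total is one defensible lead outcome among several.

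**What to change.** Make one of two changes before unblinding.

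1. **Minimum.** Reword the sentence to say that the rule limits only the additional error from visit 3 and that the visit 2 tests are unadjusted. This costs nothing but gives up the claim of overall control.
2. **Better: make the claim true.** Name one score per construct, state whether hypothesis 1 needs both caregiver outcomes or either, and apply a pre-specified procedure to the visit 2 family. One option is a fixed sequence, for example HFS-PYC total first at the full .05, then one named PIP score, HbA1c and time in range, with confirmatory claims ending at the first non-significant result. Another is Holm. Report the remaining scores with confidence intervals only. If the analysis plan already contains such a procedure, align the article's sentence with it.

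**Cost.** In a fixed sequence the first test keeps its full power, but later outcomes may end as non-confirmatory. Holm costs some power per outcome. Its hardest step with four outcomes is .0125. Take 0.4 SD, 40 groups of 3.6 families, residual variance 1 − .72² = .48 and an ICC of .10 within that residual. The standard error is then √(.48 × (.10 + .90/3.6) × 2/20) = .13, and power in a t test on 38 degrees of freedom falls from about 85% to about 68%. That figure depends on how the Power Analysis variances are read.
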